## Objective

2

The aim of this study is to evaluate the effectiveness of an alternative sports program in a school setting, compared to standard physical education, on physical fitness, body composition, motor skills, and enjoyment of physical activity among elementary school students aged 11–12.

## Materials and methods

3

### Study design

3.1

The study adopts a cluster-randomized controlled trial (cRCT) design with repeated measures and parallel groups (three intervention groups and three control groups), following a quantitative approach. This protocol was developed in accordance with the SPIRIT guidelines for clinical trial protocols (24). The trial will be reported following the CONSORT statement and its extension for cRCTs (25). The overall study design and allocation process are illustrated in Figure 1.

**Figure 1 fig1:**
[figure not shown]
Standard protocol items: recommendations for intervention trials (SPIRIT) (24). −t_1_, school and participant enrollment; 0, group assignment and baseline assessments (weight, height); t_1_–t_8_, active intervention periods; assessments at t_1_ and t_8_; t_9_, follow-up assessments (weight, height).

Authorization to conduct the intervention will be obtained from the participating schools, and parents or legal guardians will provide written informed consent prior to student participation. Upon completion of the study, families will receive a summary report of their children’s assessment results.

### Sample size

3.2

The trial is designed as a cRCT with the class group as the unit of randomization. The minimum clinically relevant difference in body fat percentage has been defined as 3 percentage points (*Δ* = 3), with an estimated standard deviation of 5. A significance level of *α* = 0.05 (two-sided) and a statistical power of 80% were assumed. An average group size of *n* = 35 students and a loss-to-follow-up/dropout rate of 15% were considered. Based on recent literature on randomized controlled trials (RCTs) in school-aged children, an intracluster correlation coefficient (ICC) of 0.03 was assumed (18).

With these assumptions, approximately 44 students per group are needed in a single trial. Adjusting for the cluster effect with an ICC = 0.03, the group size increases to approximately 88 students. Therefore, considering a 15% attrition rate, the final group size is approximately 104 students. To achieve this with groups of an average size of 35, 3 courses/groups per cohort (6 groups in total) will be required, implying 210 enrolled students (105 in the intervention group/105 in the control group). The flow of participants throughout the study is summarized in Figure 2.

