**Figure 2 fig2:**
[figure not shown]
Study flowchart. P: Public administration; PS: Subsidized private administration; PU: Unsubsidized private administration.

Although body composition is not the primary outcome, it was selected as the reference variable for sample size calculation due to its high sensitivity and the existence of well-established thresholds of clinical relevance in the academic literature (26, 27). As it is a variable with greater inter-subject variability in short- to medium-term interventions, the sample size derived from it acts as a conservative estimate. This approach ensures robust statistical power (>80%) to detect significant effects not only in body composition but also in secondary variables with lower sample size requirements, such as motor competence or enjoyment (28).

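### The 80% and above-80% power claims are not supported: the calculation makes no allowance for only six randomised classes, paired within three schools

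*Protocol article*

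**What the plan says.** All references are to the protocol article. Section 3.2 fixes the randomised unit: "The trial is designed as a cRCT with the class group as the unit of randomization". The target is body fat: "The minimum clinically relevant difference in body fat percentage has been defined as 3 percentage points", "with an estimated standard deviation of 5". The error rates are alpha 0.05 ("two-sided) and a statistical power of 80% were assumed"), the ICC is 0.03, the average class has 35 students, and "a loss-to-follow-up/dropout rate of 15% were considered". From about 44 students per arm it moves on: "Adjusting for the cluster effect with an ICC = 0.03, the group size increases to approximately 88 students". Attrition raises this to about 104, and the conclusion is: "To achieve this with groups of an average size of 35, 3 courses/groups per cohort (6 groups in total) will be required", giving 105 enrolled per arm and 210 in all.

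The paragraph after Figure 2, still in 3.2, concedes that body composition is not the primary outcome. It nevertheless says "This approach ensures robust statistical power (>80%) to detect significant effects", and extends this beyond body composition to motor competence and enjoyment.

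Section 3.3 places one intervention and one control class in each of three schools. Section 3.13.2 tests the group × time interaction, which is the difference between arms in change from baseline.

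**The concern.** A design effect inflates the variance for within-class correlation. It does not account for how few classes there are from which to estimate the between-class variance. With many clusters that hardly matters and normal quantiles serve. With three classes per arm, an unpaired class-level comparison has 2 × (3 − 1) = 4 df and a two-sided 5% critical value of 2.78. A comparison of classes within schools has 3 − 1 = 2 df and a critical value of 4.30. Section 3.2 mentions neither degrees of freedom nor any small-cluster correction.

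At stake is a headline property of the design. Someone judging whether six classes suffice, or how much a non-significant result tells them, will rely on the 80% figure. Because the article extends the claim to motor competence, the problem reaches the primary outcome too: the limit of six classes applies to every outcome.

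**Working it through.** **Inputs (section 3.2 unless noted).** Δ = 3; SD = 5; alpha 0.05 two-sided; power 80%; 35 per class; ICC 0.03; loss 15%; three classes per arm, paired within three schools (3.3).

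**Step 1: reproduce the plan's figures.**
- Individual level: n = 2 × 25/9 × (1.960 + 0.842)² = 43.6, rounded up to 44.
- Design effect: 1 + 34 × 0.03 = 2.02; 43.6 × 2.02 = 88.1.
- Attrition: 88/0.85 = 103.5, i.e. 104. Three classes of 35 give 105.

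Every figure matches. The article does not name the normal approximation; it is inferred from this match and from the absence of any small-cluster correction.

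**Step 2: same inputs, t reference.** SE = √(2 × 25 × DE / N per arm), noncentrality = 3/SE, power from the noncentral t.

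| Analysed per arm | DE | SE | Noncentrality | Normal | t, 4 df | t, 2 df |
|---|---|---|---|---|---|---|
| 88 | 2.02 | 1.071 | 2.80 | 80.0% | 56.4% | 35.2% |
| 89.25 (15% loss; 29.75 per class) | 1 + 28.75 × 0.03 = 1.8625 | 1.021 | 2.94 | 83.6% | 60.2% | 37.6% |
| 105 (no loss) | 2.02 | 0.981 | 3.06 | 86.4% | 63.5% | 39.8% |

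A simulation of class means (200,000 replicates) at 29.75 per class gave 60.4% and 37.6%.

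**Step 3: credit for pairing.** The 2-df column charges the loss of degrees of freedom for pairing but credits no gain, so it is a lower bound. If pairing removed all between-class variance, the SE would be √(2 × 25/89.25) = 0.748, the noncentrality 4.01 and the 2-df power 56.6%. Keeping only the within-class share of the variance (25 × 0.97) gives an SE of 0.737 and 57.6%. The upper end is therefore about 57%.

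**Step 4: difference detectable with 80% power, after 15% loss.** The noncentrality needed is 3.76 on 4 df and 5.65 on 2 df.
- 4 df: 3.76 × 1.021 = 3.8 points.
- 2 df, no gain from pairing: 5.65 × 1.021 = 5.8 points.
- 2 df, all between-class variance removed: 5.65 × 0.748 = 4.2 points.

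**Step 5: what SD 5 means.** Steps 2 to 4 take SD 5 as the SD of the analysed quantity. If it is cross-sectional and change is analysed, the SD of change is 5 × √(2(1 − r)), where r is the pre-post correlation. The article gives no r, so the values below are assumptions. ICC 0.03 is kept for change, with 29.75 per class and no gain from pairing.

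| Assumed r | SD of change | t, 4 df | t, 2 df |
|---|---|---|---|
| 0.5 | 5.00 | 60% | 38% |
| 0.7 | 3.87 | 81% | 53% |
| 0.8 | 3.16 | 93% | 67% |
| 0.9 | 2.24 | 99.7% | 88% |

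Power reaches 80% at r of about 0.70 on 4 df and about 0.87 on 2 df. Below r = 0.5 the SD of change exceeds 5, and power is lower than in Step 2.

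**The case against.** The strongest reply is that Step 2 prices a different analysis from the planned one. Section 3.13.2 tests change from baseline, and a strong pre-post correlation could bring power to 80% or well above. This stands. A reader might infer from Step 2 that the trial's power simply is about 60% or lower; the documents do not support that, because 3.2 does not say whether SD 5 is cross-sectional or of change. But the reply does not rescue the claim as written. Section 3.2 states no correlation and takes no credit for one, and its own steps do not lead to 80% with six classes.

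A second reply is that the planned mixed model has more nominal power. Its only random intercept is for school, and each school contributes to both arms, so that term does not carry the between-class variance of the randomised unit. Extra power obtained by leaving that variance out would cost type I error and cannot support the claim.

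A third is that the stated figures contain no slip. That is true: they reproduce. The fault is one of method, not arithmetic.

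Two further inferences are tempting and do not hold. With three school pairs there are only eight allocations, so a randomisation test could not give a two-sided p-value below 0.25; but the plan uses mixed models, not such a test. And one might say there is no margin for non-consent; but 3.2 already counts the 210 as enrolled, and the article gives neither class rolls nor a consent rate.

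**Conclusion.** The concern holds as a statement about support: the calculation in 3.2 does not justify 80% or above-80% power. With SD 5 taken as the SD of the analysed quantity, ICC 0.03 and 15% loss, the shortfall from 80% is about 20 percentage points on 4 df. On 2 df it is about 23 to 42 points, depending on how much between-class variance the pairing removes. The design's actual power stays open until the article says what SD 5 is. The extension to motor competence and enjoyment rests on the same calculation and is equally unsupported; nothing here says what power those outcomes do have.

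**What to change.** Keep the six classes and revise 3.2 as follows.

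1. Say whether SD 5 is cross-sectional or the SD of change, and give any pre-post correlation relied on, with its basis.
2. Restate power and detectable difference from a t reference with 4 or 2 df, matching the comparison intended, under that assumption. If SD 5 is the SD of the analysed quantity: about 60% (4 df) or 38% to 57% (2 df) for 3 points, and about 3.8 points (4 df) or 4.2 to 5.8 points (2 df) detectable with 80% power. If SD 5 is cross-sectional and change is analysed, show a range: for example, an assumed correlation of 0.7 gives about 81% on 4 df and 53% on 2 df.
3. Remove the unqualified 80% and above-80% statements, including the extension to motor competence and enjoyment.

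The cost is a text change and a less favourable power statement. No extra classes or students are needed.

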**Figure 2 fig2:**
[figure not shown]
Study flowchart. P: Public administration; PS: Subsidized private administration; PU: Unsubsidized private administration.

Although body composition is not the primary outcome, it was selected as the reference variable for sample size calculation due to its high sensitivity and the existence of well-established thresholds of clinical relevance in the academic literature (26, 27). As it is a variable with greater inter-subject variability in short- to medium-term interventions, the sample size derived from it acts as a conservative estimate. This approach ensures robust statistical power (>80%) to detect significant effects not only in body composition but also in secondary variables with lower sample size requirements, such as motor competence or enjoyment (28).

### Randomization and blinding

3.3

Randomization will be conducted at the school and class levels. Urban schools in the city of Talca, Chile, will be randomly selected using a computer-generated sequence. Three schools will be included, representing different administrative types within the Chilean education system: a public school, a subsidized private school, and a private school.

Within each participating school, two intact classes will be included. One class will be randomly assigned to the intervention group (IG) and the other to the control group (CG), resulting in parallel groups within the same educational setting.

Due to the nature of the school-based intervention, it will not be possible to blind participants, teachers, and intervention staff. However, data management and statistical analyses will be conducted using anonymized datasets to minimize potential bias.

To ensure treatment fidelity and minimize experimenter bias, the intervention will be implemented by an external researcher who is specialized and specifically trained in the study protocol (29). In contrast, the control group will maintain its usual curriculum as led by the school’s regular teacher. This design not only allows for rigorous standardization of the independent variable but also ensures that the control group reflects real-world conditions, thereby preserving the ecological validity of the study in naturalistic school settings (30, 31).

### Inclusion criteria

3.4

Students aged 11–12 who are in the sixth grade of elementary school and whose parents provide written informed consent for their participation.

### Exclusion criteria

3.5

Students with a medical condition that prevents them from participating in alternative sports or those with a cognitive disability will be excluded. These criteria are used because the effect of the intervention on the study variables (physical fitness, motor skills, physical activity level, and enjoyment) depends on the students’ physical and psychological readiness to perform the various motor tasks.

### Recruitment, participants, and assignment

3.6

Educational institutions will be randomly selected and invited to participate through an initial email contact with school principals, followed by a telephone follow-up 1 week later. Subsequently, a member of the research team will meet with interested principals to explain the study’s objectives, procedures, and participation requirements. Once institutional approval is obtained, informational meetings will be scheduled with teachers and students at the selected schools.

Each participating school will provide two class groups, with one group assigned to the IG and the other to the CG. Schools that agree to participate will receive written information in plain language, along with informed consent forms for parents or legal guardians. Recruitment will take place over a two-month period in 2026 at three elementary schools in the city of Talca, Chile.

Following institutional approval, detailed information about the study will be provided to students in the selected classes. Only students whose parents or legal guardians provide written informed consent and who give their assent will be included in the data collection. Participation will be voluntary, and students may withdraw from the study at any time without academic consequences.

### Intervention

3.7

#### Intervention group (IG)

3.7.1

The IG will receive a pedagogical intervention based on the Teaching Games for Understanding (TGfU) model (14), specifically adapted for teaching alternative sports (32) (Figure 3).

**Figure 3 fig3:**
[figure not shown]
Diagram of the methodological sequence for teaching alternative sports, adapted from Morales-Campo et al. (15), and modified by the authors.

To maximize treatment fidelity and minimize inter-instructor variability, all sessions will be conducted by an external physical education instructor who has been thoroughly trained in the research protocol. This methodological strategy ensures standardized application of the pedagogical model, regardless of the usual teaching practices at each participating school.

The intervention consists of four teaching units, each lasting 2 weeks, focused on: flag football, ultimate frisbee, korfball, and kin-ball. These disciplines were selected for their low requirement for prior specialization, their potential for developing motor skills, and their ability to promote gender equity and social inclusion (33–35).

The pedagogical progression will follow a structure of increasing complexity in three phases: (1) initiation through simplified rules and general game situations; (2) development of tactical awareness and motor execution through modified games; and (3) integration into real game scenarios with an emphasis on decision-making. For example, in ultimate frisbee, the progression moves from basic throwing and catching skills in dynamic contexts to situations of numerical superiority in confined spaces, culminating in full-format games where intelligent use of space and offensive-defensive transitions are prioritized.

#### Control group (CG)

3.7.2

The CG will participate only in the baseline and post-intervention assessments, maintaining its regular physical education curriculum led by its regular teacher, with no changes to the existing lesson plans or teaching methodology. The sessions will be governed by the National Curriculum Standards currently in effect in Chile, specifically in the development of Unit 2: Individual and Team Games and Sports (11).

The curriculum offered in the CG will include traditional sports (i.e., basketball, soccer, and handball) using a traditional technical-pedagogical approach, characterized by an emphasis on the acquisition of fine motor skills and basic tactical patterns. Lessons will predominantly employ direct instruction strategies (command style), based on teacher demonstration, repetitive practice of tasks (drills), and prescriptive corrective feedback. Equivalence in activity volume (frequency and duration of sessions) between the IG and the CG will be ensured to guarantee group comparability.

It should be noted that the design of this study does not aim to contrast ‘effective’ teaching with ‘ineffective’ teaching. On the contrary, it is recognized that well-structured traditional Physical Education can promote motor learning through skill progression (36). Therefore, the objective of this comparison is to determine whether a comprehensive teaching model (TGfU) integrated with alternative sports provides incremental or superior benefits in motor competence and health compared to the standard pedagogical practice (usual care) of the educational system (37).

#### RENUÉVATE program

3.7.3

Each session will last 90 min and will follow a standardized structure consisting of three clearly differentiated phases:

##### Warm-up (15 min)

3.7.3.1

The initial phase will include general joint mobility exercises and sport-specific activities designed to prepare students for the corresponding alternative sport. Activities will be performed at a low to moderate intensity, equivalent to 50–60% of maximum heart rate (HRmax) and a rate of perceived exertion (RPE) between 9 and 11. The objective of this phase is to progressively activate the musculoskeletal and cardiovascular systems, reduce the risk of injury, and facilitate preparation for learning.

##### Main part (65 min)

3.7.3.2

This phase will focus on practicing the alternative sport through modified game situations and technical-tactical progressions, in line with the TGfU approach. Tasks will be designed to promote decision-making, game understanding, and motor execution, maintaining a moderate to vigorous intensity (65–80% of HRmax; RPE 12–15) (4).

Active recovery periods will be incorporated between activities to promote recovery and continuity of practice. To validate the intensity achieved, wrist-based heart rate monitors will be used on a subsample comprising 25% of the participants.

##### Cool-down (10 min)

3.7.3.3

The session will conclude with low-intensity recovery activities, including relaxation exercises, stretching, and a brief group reflection on motor learning and the values addressed during the session. This phase will be conducted at a light intensity, below 50% of HRmax, with a RPE ≤ 9.

### Implementation, intervention fidelity, and teacher training session

3.8

Before the start of the intervention, the physical education teacher assigned to the IG will receive a specific training session delivered by the research team. This training will last approximately 45–60 min and will cover the theoretical foundations of the RENUÉVATE program, the TGfU methodology applied to alternative sports, the intervention’s objectives, the organization of the sessions, and instructions for the proper implementation and evaluation of the program. Once the training is complete, the necessary instructional and support materials for carrying out the intervention will be provided. To ensure proper implementation and adherence to the RENUÉVATE intervention protocol, a member of the research team will supervise the initial phases of the process. During the first weeks of the intervention, the researcher will provide technical and methodological support to the physical education teacher responsible for the intervention group, answering their questions, adjusting activities as necessary, and providing ongoing feedback.

In the initial phase, the teacher will conduct the sessions according to the established plan for each alternative sport, while the researcher will observe the classes and offer suggestions aimed at optimizing the application of the TGfU methodological approach adapted to alternative sports. Subsequently, the teacher will conduct the sessions independently, maintaining ongoing communication with the research team to address any issues that arise during the program’s implementation.

The fidelity of the intervention will be assessed through direct observation using a standardized checklist based on the key components of the TGfU model (e.g., emphasis on modified play, tactical challenge questions, and transitions). An external observer will evaluate 20% of the sessions at random. In addition, a session log self-reported by the instructor will be used.

Decision-making based on fidelity will be structured as follows: if the fidelity score falls below 80% in a session, an immediate retraining session for the instructor will be initiated prior to the next teaching unit. If deviations persist, data from that specific group will be analyzed using “intention-to-treat” and “per-protocol” analyses to assess the impact of the instructional dose on final outcomes.

### Procedures, outcome measures, and data collection

3.9

Assessments will be conducted at two time points: at baseline, prior to the start of the intervention (Session 1), and at the end of the program (Session 16). At both time points, anthropometric measurements, physical fitness, motor competence, objectively and subjectively assessed physical activity levels, and enjoyment of physical activity will be collected.

Data collection will be carried out by a team of trained research assistants, who will receive prior instruction from the research team through specific training sessions designed to ensure the correct application of the assessment instruments and the standardization of procedures. The evaluators will have no prior relationship with the students, and their role in the study will be limited exclusively to data collection, in order to minimize any potential bias in the evaluation.

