**Methods:**

A cluster-randomized controlled trial will be conducted among 11- to 12-year-old schoolchildren. Schools will be selected at random, and within each school, two classes from the same grade will be assigned to the intervention or control groups. The intervention will consist of an eight-week instructional unit (16 sessions) based on four alternative sports (flag football, ultimate frisbee, korfball, and kin-ball) taught using the Teaching Games for Understanding approach. The control group will continue with the regular physical education curriculum. Physical fitness, motor competence, and enjoyment of physical activity will be assessed as primary outcomes, while physical activity levels and body composition will be considered secondary outcomes. All variables will be assessed before and after the intervention. Primary analyses will follow the intention-to-treat principle using mixed-effects models to account for clustering (students within schools). The effects of the intervention will be estimated using the group × time interaction. Analyses will be performed using SPSS v28 and R v4.3.

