#### Primary analysis (intention-to-treat)

3.13.2

The primary analysis will be conducted according to the intention-to-treat (ITT) principle, including all participants as they were originally assigned, regardless of their adherence to the intervention. To estimate the effects of the RENUÉVATE intervention, mixed-effects regression models will be used to adequately account for the cRCT design (students nested within schools).

The effects of the intervention will be assessed through the group × time interaction, which represents the differences between groups in changes from baseline (Session 1) to post-intervention (Session 16). For continuous outcomes, including motor skills, physical fitness, enjoyment, physical activity levels, and body composition, linear mixed-effects models will be applied. For dichotomous outcomes, where applicable, generalized linear mixed models (GLMM) with a logit link function will be used.

All models will include group (intervention vs. control), time (baseline and post-intervention), and their interaction as fixed effects. Age and sex will be included as covariates. A random intercept will be specified for school to account for intraclass correlation within clusters.

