#### Sensitivity analysis (per protocol)

3.13.3

A per-protocol sensitivity analysis will be conducted, including only participants who attend at least 85% of the intervention sessions and complete both measurement points. The same mixed-effects modeling approach described for the ITT analysis will be applied to assess the robustness of the findings.

Patterns and proportions of missing data will be examined prior to analysis. When missing data exceed 5%, multiple imputations will be performed using chained equations under the assumption that data are missing at random. The imputation model will include all variables used in the primary analyses.

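### Multiple imputation is described under the per-protocol analysis and names only the primary-analysis variables; it should be tied to the ITT set and include attendance by arm

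*Protocol article*

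**What the plan says.** Timing: the abstract states "The intervention will consist of an eight-week instructional unit (16 sessions", so Session 16 is the last lesson. Section 3.9 sets the second assessment "and at the end of the program (Session 16", and section 3.13.2 uses the same label for the post-intervention time point.

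ITT: section 3.13.2 promises an analysis "including all participants as they were originally assigned, regardless of their adherence to the intervention". The model has group, time, their interaction and a random intercept for school, and "Age and sex will be included as covariates". That section gives no rule for missing outcomes.

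Missing data: the rule is in section 3.13.3, headed as the per-protocol sensitivity analysis. That set requires at least 85% attendance and both measurements. The next paragraph reads "When missing data exceed 5%, multiple imputations will be performed using chained equations under the assumption that data are missing at random", followed by "The imputation model will include all variables used in the primary analyses".

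Attendance: it defines the per-protocol set, and the Discussion lists its monitoring among the safeguards. It is not in the primary model and is not named for the imputation.

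**The concern.** Two things in the printed text do not fit together well. First, the imputation rule is placed with a set in which, by definition, no endpoint is missing. The analysis that needs it, ITT, has no rule of its own. Second, if the rule is meant for ITT, the stated imputation model carries only what the primary model already carries. It then rests on essentially the same missing-at-random condition as the mixed model and adds little to it.

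The variable most likely to add something is attendance. A pupil who often misses physical education is more likely to be absent on the day of an assessment timed at a lesson. In the intervention group attendance is also the dose received. It may therefore relate to motor competence or enjoyment differently in the two arms. If so, and if the baseline score does not already carry that link, the measured pupils give a somewhat too favourable picture of the group × time effect.

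**Working it through.** **Inputs from the article.** Loss 15%, 105 pupils per arm, class size 35, ICC 0.03, difference 3, SD 5 (section 3.2). The 3 points of body fat equal 3/5 = 0.6 SD, used below as the true effect.

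**The plan's own figures.** About 44 per arm without clustering; design effect 1 + 34 × 0.03 = 2.02; 44 × 2.02 = 88.9 (88 in the article); 88/0.85 = 103.5, so 104. These reproduce and are not in dispute. Expected loss is 105 × 0.15 = 15.75, about 16 pupils per arm. That is above the 5% trigger, so on the plan's own assumption imputation will be used.

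**Assumptions of the illustration.** Attendance is standardised. The log-odds of a missing endpoint rise by 1.5 for each SD of poorer attendance, calibrated to 15% missing. The correlation of attendance with outcome is r(IG) and r(CG). Baseline correlates 0.65 with the endpoint and is in the imputation model. A share s of the attendance–outcome link runs through baseline.

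**Formula.** Under these assumptions the measured pupils have mean attendance about 0.175 SD above the whole arm. Imputing from baseline without attendance leaves

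bias ≈ 0.175 × (r(IG) − r(CG)) × (1 − s), in SD units.

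| r(IG) / r(CG) | s = 0 | s = 0.5 | s = 1 |
|---|---|---|---|
| 0.2 / 0 | 0.035 | 0.018 | 0 |
| 0.3 / 0 | 0.053 | 0.026 | 0 |
| 0.4 / 0 | 0.070 | 0.035 | 0 |
| 0.3 / 0.2 | 0.018 | 0.009 | 0 |
| 0.3 / 0.3 | 0 | 0 | 0 |

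A simulation with 2,000,000 pupils per arm agrees within 0.003. For example, at s = 0 the estimates for a true 0.60 were about 0.64, 0.65 and 0.67 in the first three rows. Imputing within arm from baseline and attendance returned 0.60 in every row.

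**Against the precision of the trial.** The standard error of a difference in SD units is about √(2 × 2.02/(105 × 0.85)) = √(4.04/89.25) = 0.21. The largest bias in the table, 0.07, is one third of that.

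**A second check on the body-fat scale.** Assume mean attendance of 85%, an effect proportional to attendance (true ITT effect 3 × 0.85 = 2.55 points) and 15% missing. If absence follows each pupil's own attendance rate, the estimate is 2.59 without attendance and 2.55 with it. If every low attender is missing, it is 2.67 without and 2.57 with. The bias without attendance is thus 0.04 to 0.12 points, or 0.01 to 0.02 SD.

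**The case against.** The strongest reply is that the text is workable as it stands. The sentence on the imputation model sets a minimum and does not bar auxiliary variables, which are often left to an analysis plan. The paragraph mentions the primary analyses, so it can be read as covering ITT despite its heading. Baseline is in the model and may carry most of the link between attendance and outcome. The bias cancels if the arms behave alike, and it is small beside the standard error.

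Most of this stands, and it limits the point to a modest improvement. It does not remove it. The article chose to state the content of the imputation model, and the heading it chose does not match the set that needs the rule. Both can be corrected in the same two sentences.

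A reader might go further and infer that pupils who stop attending have no endpoint. The article does not say so. Session 16 works as a time label, research assistants rather than the lesson teacher collect the data, and nothing makes measurement conditional on taking part in lessons. The consent wording, "students may withdraw from the study at any time without academic consequences", concerns leaving the study, not missing lessons. Low adherence and absence on one day also differ: 85% of 16 is 13.6, so a pupil can miss two lessons and stay in the per-protocol set. Only accelerometry is tied to lessons by design, as the devices are worn only there.

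**Conclusion.** The point holds as a modest weakness in a stated method. The imputation rule is attached to the wrong set and does not name attendance, so missing at random is less plausible for ITT than it need be. The size is 0 to about 0.07 SD with 15% missing and correlations of 0.2 to 0.4 in the intervention group against 0 in the control group. It is zero if the arms behave alike or if baseline carries the whole link. The 15% is the article's own loss rate; the correlations, the missingness slope and the baseline correlation are assumptions.

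It would be tempting to conclude that the ITT promise is broken. The documents do not support that: all pupils are kept as assigned, and missing outcomes are handled under a stated assumption.

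**What to change.** In section 3.13.3, or better by moving the paragraph to section 3.13.2:

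1. State that multiple imputation applies to the ITT set.
2. Add the number of physical education lessons attended, in both arms, to the imputation model as an auxiliary variable interacting with group, or impute separately by arm.

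The analysis cost is nil. The one condition is that attendance is logged in the control classes as well as the intervention classes; the article lists monitoring of attendance but does not say expressly that it covers both.

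The change has a limit: if no low attender were measured, attendance would only extrapolate from attenders, as the 2.57 against 2.55 above shows. A further full battery at the later contact in the Figure 1 legend, given there as "follow-up assessments (weight, height", is not part of this recommendation. It would be an extra assessment, and arrangements for absentees are operational detail that an article may leave to the full protocol.
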